#### Active range of motion

Patients will have their AROM (pain-free) measured for shoulder flexion, extension, and abduction on both arms using goniometry [17]. AROM for each action will be measured twice. The measurements per action per arm will be averaged for data analysis.

#### Mid upper arm circumference measurement

The MUAC will be specifically noted by measuring the arm circumference at the mid-point between the tip of the shoulder and tip of the elbow (acromion and olecranon process) [18]. Each measure will be taken twice on both arms by a trained member of the research team. The measurement per arm will be averaged for analysis.

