### Patients (participants)

We plan to recruit up to 40 patients (20 per group) from the Singapore General Hospital (SGH) and National Cancer Centre Singapore (NCCS), where they will be receiving preoperative, surgical, postoperative, and rehabilitation care. Patients are recruited from multiple clinics, under a single healthcare system in Singapore, consisting of a multi-ethnic Asian population.

Patients are eligible to participate in the trial when they meet the following four criteria: (i) female 21 years of age and older, (ii) undergoing or underwent a recent unilateral breast surgery (wide excision or simple mastectomy) with lymph nodes removed, (iii) speak and write English or Mandarin, and (iv) no past or active psychiatric condition as assessed by a referring clinician. Patients are ineligible to participate if they meet one of the following four criteria: (i) having breast reconstruction, (ii) having legal blindness or severe visual impairment, (iii) having life expectancy of less than 3 months, or (iv) having previous upper limb injury or conditions that limit upper limb range of motion (shoulder flexion (< 150°) or elbow extension/flexion (< 0/145°) respectively).

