### Procedure (recruitment, allocation, and data collection)

Potential participants will be approached by a breast care nurse and/or doctor (who will be providing the patient care related to breast cancer and mastectomy) during their pre-operation counseling session. These nurses and doctors will provide their patients with our study invitation letter. The patients will be asked to contact the research team directly using the contact information provided in the study invitation letter if they are interested in the study. Alternatively, if the patients agree, the nurses and doctors will obtain patients’ contact information (i.e., first or last name with an email address or a phone number only) which will be forwarded to the research team to initiate contact.

If patients agree to participate in the trial, they will complete the informed consent process with a trained member of the research team. The informed consent process can occur anytime between the time of their surgical consultation and 5 days post-surgery. After the informed consent process is completed, patients will self-assign themselves to the intervention group (tele-rehabilitation) or the control group (usual rehabilitation). The prescription and administration of drain care (education) and rehabilitation for both groups of patients are determined and managed by an assigned nurse and therapist per usual practice.

All consented patients will be asked to complete two assessments with a trained member of the research team at their home (or at the university where the research is being conducted). The first (baseline) assessment will take place approximately 3-week post-surgery after completing drain-care (education) period (i.e., pre-rehabilitation assessment). The second (exit) assessment will take place after completing a 12-week physical rehabilitation period (i.e., post-rehabilitation assessment) (refer to Fig. 1 for an overview of the study outlining the timing of baseline and exit assessments). No patients, care providers, assessors, or analysts will be blinded. Any adverse events, although unanticipated, will be discussed within the team and reported to the National Healthcare Group Domain Specific Review Board within seven calendar days.

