### Tele-rehabilitation (intervention) and usual care (control)

Patients in the intervention group will have the tele-rehabilitation system for up to 15 weeks. The first 3 weeks will be for drain care video education (post-mastectomy) and the following 12 weeks will be for physical tele-rehabilitation (including shoulder and arm exercise, and self-arm massage). During the physical rehabilitation period, patients (in the tele-rehabilitation group) and/or an assigned occupational therapist may arrange up to five 30-min video conferences (the number of sessions will be determined by an assigned therapist, as per request or per need of each patient).

Patients in the control group will receive the same instructions (for drain care education as well as shoulder and arm exercise and self-arm massage) by their multidisciplinary rehabilitation team but without remote support with the tele-rehabilitation and tele-drain care system. Their drain care education and physical rehabilitation sessions will instead take place in-person at their clinic with their assigned nurse and therapist (refer to Table 1 for brief descriptions of drain care education with a nurse and rehabilitation with an occupational therapist).

**Table 1 Tab1:** Brief descriptions of drain care education with a nurse and rehabilitation with an occupational therapist

Drain Care Education	Arm and Shoulder Massage	Exercise
Drain care education provides information on how to manage the drainage devices and fluids collected post-mastectomy. These include proper and safe physical handling of the drainage devices, and proper sequences to empty, measure, and dispose fluids from the drainage devices.	Arm and shoulder massage are performed with the aim of managing edema (reducing arm swelling) post-mastectomy. They consist of a series of actions to facilitate pushing fluid out of the affected areas back into the bloodstream, therefore preventing fluid accumulation and limb swelling.	The exercises are performed with the aim of maintaining the active range of motion of the upper limbs, which concurrently helps to drain fluid. The exercises involve deep breathing and a series of movements including shoulder elevation, retraction, protraction and flexion, and elbow flexion and extension.

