The secondary outcomes of this trial are upper extremity functioning, perceived health, and QoL. Upper extremity functioning will be measured by shoulder active range of motion (AROM) [17], arm circumference (AC) [18], the Quick Disabilities of Arm, Shoulder & Hand (QuickDASH) [19]. Perceived health will be measured by the EuroQoL-5D (EQ-5D-3L) [20] and QoL will be measured by the European Organization for Research and Treatment of Cancer Quality of Life Questionnaire Core 30 (EORTC QLQ-C30) [21]. For the secondary outcomes, all patients will be asked to complete all five measures with a trained member of the research team at both pre- and post-rehabilitation assessment. We hypothesize that both groups will show similar improvements across all secondary outcome measures.

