### Analysis

For quantitative data, we will report means and standard deviations for parametric data, medians and inter-quartile ranges for non-parametric data, and numbers and percentages of all categorical variables for descriptive purposes. Further, inferential statistics (e.g., *T* test, chi-square test) will be performed to compare the outcome measures between the two groups. We will perform a random data (entry) check by the secondary data management personnel (who did not collect the data or complete the initial data entry). Missing data will not be replaced or imputed.

For the qualitative data, we will conduct inductive analysis that involves discovering patterns, themes, and categories related to the lived experience of breast cancer diagnosis, rehabilitation, and recovery process (using five steps of qualitative data analysis outlined by Miles and Huberman) [28].

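### The protocol averages limb readings per arm but does not name the operated arm as the outcome or use the unoperated arm as the reference for swelling

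*Protocol article*

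**What the plan says.** Eligibility in the protocol article (Patients) requires "undergoing or underwent a recent unilateral breast surgery (wide excision or simple mastectomy) with lymph nodes removed", so every participant has one operated and one unoperated side.

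For girth (Mid upper arm circumference measurement): "Each measure will be taken twice on both arms by a trained member of the research team". The derived variable follows: "The measurement per arm will be averaged for analysis". Active range of motion is treated in the same way: "The measurements per action per arm will be averaged for data analysis".

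The Measurements section places both among the secondary outcomes, under upper extremity functioning, and has all secondary measures taken before and after rehabilitation. On timing, the Procedure section states: "The first (baseline) assessment will take place approximately 3-week post-surgery after completing drain-care (education) period".

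The Analysis section says that "inferential statistics (e.g., *T* test, chi-square test) will be performed to compare the outcome measures between the two groups". It names no arm, no between-arm contrast and no baseline adjustment. Allocation is by patient preference (Study design), with 10 to 20 patients per group (A power calculation).

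**The concern.** Swelling is something the intervention is meant to change. Table 1 says "Arm and shoulder massage are performed with the aim of managing edema (reducing arm swelling) post-mastectomy". Girth of one arm is only an indirect measure of swelling, because it also reflects body size and any weight change over the 12 weeks, and those affect both arms.

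Three features of the design make this matter more than usual. Patients choose their group, so randomisation does not balance body size or weight change. The groups are small. There is no pre-surgical reading, so the unoperated arm is the only reference within the patient for swelling already present at the first assessment.

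A t test on per-arm averages could then show a group difference that is really one of body size or weight, or could hide a difference in swelling. The team expects similar improvement in both groups on all secondary outcomes, and variance unrelated to swelling makes a finding of no difference less informative. The pilot data are also meant to inform the size of the main trial, so an SD for raw girth could be carried into that calculation.

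**Working it through.** **No figure to reproduce.** The document gives no SD, effect size, alpha, power or between-arm correlation for the limb measures. The 10 to 20 per group come from cited rules of thumb. Everything numerical below rests on assumed inputs.

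**What each comparison estimates.** Write girth at a visit as B + S on the operated arm and B on the unoperated arm, where B is the body-size part and S is swelling. Let D( ) be the difference in group means.

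- t test on operated-arm exit girth: D(B exit) + D(S exit). Body size stays in.
- t test on operated-arm change: D(B exit - B baseline) + D(S exit - S baseline). Stable body size cancels; weight change stays in.
- Operated minus unoperated at exit: D(S exit). Both drop out, and adjusting for the same difference at baseline allows for swelling present at 3 weeks.

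The last line assumes that B is shared by both arms and that treatment does not alter the unoperated arm.

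**Precision.** Adjusting for a covariate that has correlation r with the outcome multiplies residual variance by 1 - r². With equal SDs in the two arms, a simple difference multiplies it by 2(1 - r). The gap is 2(1 - r) - (1 - r²) = (1 - r)², which is never negative. Adjustment is therefore never the less precise of the two, apart from a lost degree of freedom, and the difference gains precision only if r exceeds 0.5.

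Take 16 completers per group (20 × 0.80, the completion criterion) and divide by each factor for the equivalent number:

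| assumed r | 1 - r² | 16 acts like | 2(1 - r) | 16 acts like |
|---|---|---|---|---|
| 0.3 | 0.91 | 17.6 | 1.40 | 11.4 |
| 0.5 | 0.75 | 21.3 | 1.00 | 16.0 |
| 0.7 | 0.51 | 31.4 | 0.60 | 26.7 |
| 0.8 | 0.36 | 44.4 | 0.40 | 40.0 |

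**Illustration for the pilot.** Assume SD 3 cm, a true difference of 2 cm, 20 per group, two-sided alpha 0.05 and the normal approximation. For the operated arm alone, 2 / (3 × √(2/20)) = 2.11, and power is Φ(2.11 - 1.96) = 56%. On the between-arm difference the SD becomes 3 × √(2(1 - r)). Power is then 43% at r = 0.3, 56% at 0.5, 78% at 0.7 and 92% at 0.8.

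**Illustration for the main trial.** For a 1 cm difference at 80% power, n per group is 2 × (1.96 + 0.84)² × 3² / 1², which rounds up to 142 on the operated arm alone. Multiplying by 2(1 - r) gives 198 at r = 0.3, 142 at 0.5, 85 at 0.7 and 57 at 0.8.

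**The case against.** The strongest objection is that the girth sentence only explains how two repeat readings are combined. That is right. A reader might infer that each arm will be tested on its own and a between-arm contrast is excluded. The document says neither: the Analysis section gives its tests as examples, and per-arm means are the inputs that an operated-minus-unoperated difference needs. A reader might also count three movements plus girth on two arms and infer eight tests, four of them on the unoperated side. No section says that such tests will be run.

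A second objection is that defining a derived variable for a secondary outcome is normally left to an analysis plan. This has weight and keeps the point small. It does not remove it, because the article does state its analysis variables and its type of test, and a clearly better analysis of the same data is available.

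A third concerns the remedy. It is tempting to treat covariate adjustment and the between-arm difference as interchangeable; the table shows they are not (0.91 against 1.40 at r = 0.3). Adding the unoperated arm's exit value as a covariate would also condition on a post-treatment measure. The sample exercise in Table 1 uses both arms, so that value may itself respond to rehabilitation. The same caution applies to the between-arm difference, which is why it is proposed alongside the operated-arm analysis and not in its place.

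Finally, baseline and exit readings on one arm already allow within-patient change, which removes stable body size. That stands. What it leaves is weight change during the study and swelling already present at the first reading.

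**Conclusion.** The point holds in a limited form. The article names per-arm averages as the limb variables and does not say which arm is the outcome or how the unoperated arm is used. Following the text as it stands permits a raw girth comparison in small, self-selected groups, and that would not isolate swelling.

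The size cannot be taken from the document. No section shows that body size or weight change differs between the groups. The gain in precision from the between-arm difference depends on a correlation that is not given: it is a loss below 0.5 and substantial at 0.7 or above. The case for that difference rests first on what it measures and only second on precision. None of the proposed analyses removes confounding from patient choice in general.

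This is minor. No stated figure is wrong, and neither the attrition criterion nor the pilot sample size is affected. The main practical consequence is for how the pilot's girth data, and the SD taken from them, are read when the main trial is planned.

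**What to change.** Add two or three sentences to the Analysis section:

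- For girth and range of motion, the outcome is the operated arm. Groups are compared on its exit value, adjusted for its baseline value (ANCOVA).
- For girth, the operated-minus-unoperated difference at exit, adjusted for the same difference at baseline, is also reported as the measure of swelling.
- Range of motion on the unoperated side is reported descriptively.
- The observed between-arm correlation and the SD of both girth measures are reported, so that the main trial can choose between them on data.

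The cost is wording and one or two model terms; no new measurement is needed. The downside is that the between-arm difference may be less precise than the operated arm alone if the correlation is low, and may understate an effect if two-armed exercise also changes the unoperated arm. The article reports data collection as ongoing, so the choice should be fixed before the data are analysed.

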#### Self-reported upper extremity disability

The QuickDASH is an 11-item questionnaire designed to assess self-reported disability of the arm, shoulder, and hand among individuals with upper extremity disorders [19]. Its total score may range from 0 (no disability) to 100 (most severe disability) [22]. The QuickDASH is reported to have good internal consistency and test-retest reliability [19, 23].

#### Perceived health

The EQ-5D-3L is a questionnaire designed to measure self-perceived health status of individuals [20]. It consists of five dimensions (i.e., mobility, self-care, usual activities, pain/discomfort, and anxiety/depression). Individuals are asked to select one of three responses for each domain (no problems, some problems, extreme problems/unable to perform) to describe their health status. The five responses are summed and converted to a health utility index value which ranges from −0.171 to 1. Higher values indicate better health status. The EQ-5D-3L has been shown to have good test-retest reliability [24].

#### QoL

The EORTC QLQ-C30 is a QoL measure specifically designed for cancer patients. It consists of 30 items which form functional scales, a global health status/QoL scale, and symptoms scales (including financial difficulty) [21]. Scores of all scales and single-item measures range from 0 to 100 [25]. For the functioning scales and global QoL scales, higher scores indicate better functioning; for the symptom scales, higher scores indicate higher symptom burden. The EORTC QLQ is reported to have acceptable test-retest reliability and good construct validity with the 36-Item Short Form Survey [26, 27].

### Analysis

For quantitative data, we will report means and standard deviations for parametric data, medians and inter-quartile ranges for non-parametric data, and numbers and percentages of all categorical variables for descriptive purposes. Further, inferential statistics (e.g., *T* test, chi-square test) will be performed to compare the outcome measures between the two groups. We will perform a random data (entry) check by the secondary data management personnel (who did not collect the data or complete the initial data entry). Missing data will not be replaced or imputed.

For the qualitative data, we will conduct inductive analysis that involves discovering patterns, themes, and categories related to the lived experience of breast cancer diagnosis, rehabilitation, and recovery process (using five steps of qualitative data analysis outlined by Miles and Huberman) [28].

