## Methods

### Study design

This is a pilot quasi-experimental trial. Patients will be placed into the intervention group (tele-rehabilitation) or control group (usual rehabilitation care) based on their preference. The total length of the study period will be 15 weeks; patients will undergo a 3-week drain care period (post-surgery) which will be followed by a 12-week rehabilitation period. A baseline assessment will be conducted prior to commencing rehabilitation (approximately 3 weeks from the surgery) and a follow-up (exit) assessment will be conducted at the end of their rehabilitation period (approximately 12 weeks from the baseline assessment). An additional qualitative study is embedded within the trial to gain a deeper understanding of the lived experience of women who are diagnosed with breast cancer to achieve the second aim.

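### Groups are chosen by the patients, yet the only between-group tests named are unadjusted, although every secondary outcome has a pre-rehabilitation value that could be used

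*Protocol article*

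**What the plan says.** Study design, in the protocol article, sets the allocation: "Patients will be placed into the intervention group (tele-rehabilitation) or control group (usual rehabilitation care) based on their preference". The Procedure section confirms that patients assign themselves after consent, and that nobody is blinded.

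For the secondary outcomes (shoulder AROM, arm circumference, QuickDASH, EQ-5D-3L and EORTC QLQ-C30), Measurements says that "all patients will be asked to complete all five measures with a trained member of the research team at both pre- and post-rehabilitation assessment". The stated hypothesis is that both groups improve to a similar degree.

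The Analysis section gives descriptive summaries and then says that inferential statistics "will be performed to compare the outcome measures between the two groups". The t test and chi-square test are named as examples. The section does not say whether the exit score or the change is compared. It names no covariate, and it gives no caution about confounding.

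On timing, the Procedure section states: "The first (baseline) assessment will take place approximately 3-week post-surgery after completing drain-care (education) period". For the intervention group, those first three weeks already include drain-care education by video on the tele-system.

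The section on the power calculation plans 10 to 20 patients per group. It says that the pilot data will be used to size the main trial.

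**The concern.** Preference can sort patients by age, type of surgery, arm function, confidence with technology or motivation. Eligibility admits both wide excision and simple mastectomy, and any age from 21, so there is room for the groups to differ before rehabilitation starts. A plain two-sample test carries any such difference straight into the group contrast.

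The distortion can go either way. It can produce a difference where rehabilitation mode has no effect. It can also hide a real one and so appear to support the hypothesis of similar improvement. The Discussion says that the function and quality-of-life data will help design the main trial, so a distorted contrast could travel further than this pilot. The one variable most likely to reduce the problem, the pre-rehabilitation score of the same measure, is already collected, but no analysis named in the plan uses it as a covariate.

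**Working it through.** **No planned figure to reproduce.** The document gives no alpha, power, SD, effect size or margin. The 10 to 20 per group comes from cited rules of thumb, and 2 × 20 = 40 agrees with the stated maximum.

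**Inputs from the document:** preference allocation; two assessments of each secondary measure; 10 to 20 per group.

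**Assumptions (none given in the document):** scores with SD 1 at both assessments; a baseline gap g of 0.3 or 0.5 SD between the preference groups; a baseline-exit correlation ρ of 0.3, 0.5 or 0.7; a true group effect of 0; a two-sided 5% test. The exit score depends on the baseline score with slope ρ, on the same line in both groups, so the baseline score carries all of the selection.

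**Formulas**
- Exit-score contrast: bias = ρ × g.
- Change-score contrast: bias = ρ × g − g = −(1 − ρ) × g.
- ANCOVA on baseline: bias = ρ × g − ρ × g = 0 under this model.
- SE of the exit-score contrast at 20 per group: √(2/20) = 0.316.

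**Results at 20 per group** (bias from the formulas; rejection rates from 20,000 simulated trials per setting)

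| g | ρ | Exit-score bias | Rejects | Change-score bias | Rejects |
|---|---|---|---|---|---|
| 0.3 | 0.3 | 0.09 | 6.2% | −0.21 | 8.2% |
| 0.3 | 0.5 | 0.15 | 7.3% | −0.15 | 7.4% |
| 0.3 | 0.7 | 0.21 | 9.6% | −0.09 | 6.3% |
| 0.5 | 0.3 | 0.15 | 7.6% | −0.35 | 15.0% |
| 0.5 | 0.5 | 0.25 | 12.0% | −0.25 | 11.9% |
| 0.5 | 0.7 | 0.35 | 19.1% | −0.15 | 9.1% |

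In the same simulations ANCOVA had bias within 0.01 SD and rejected in about 5% of trials.

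**Smaller groups.** At 10 per group the biases are the same, but the test is less likely to detect them. The exit-score test rejects in 5.5% to 7.3% of trials with g = 0.3, and in 6.2% to 11.5% with g = 0.5.

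**Precision.** With no baseline gap, ANCOVA multiplies the variance by about 1 − ρ², which is 0.91, 0.75 or 0.51. Twenty per group is then worth 20/0.91 = 22, 20/0.75 = 27 or 20/0.51 = 39. With a 0.5 SD gap the gain is smaller, because group and baseline are correlated. At 20 per group the SD of the estimate is:
- ρ = 0.3: 0.315 against 0.316, no real gain;
- ρ = 0.5: 0.286 against 0.316, worth 20 × (0.316/0.286)² = 24 per group;
- ρ = 0.7: 0.235 against 0.315, worth 20 × (0.315/0.235)² = 36 per group.

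At 10 per group with ρ = 0.3 and g = 0.5, ANCOVA is marginally worse (0.454 against 0.446). Adding three uninformative covariates there raises the SD to about 0.50 against 0.44. This is why the main model should carry the baseline score only.

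**The case against.** **The tests are only examples, and an analysis plan may adjust.** This is fair: the list is open and the article is condensed. The point is therefore about the methods that are named. Both are unadjusted, and a better one is available from data already collected.

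**The hypothesis speaks of improvement, so change scores may be meant.** They may be. The table shows that this does not rescue the t test under the model used: the bias changes sign and does not vanish.

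**ANCOVA's zero bias is built into that model.** This is true. If the gap instead reflected a stable difference that persists in full to exit, the change score would be unbiased and ANCOVA would be off by g − ρ × g = (1 − ρ) × g. Motivation and access are also not captured by a baseline score. Adjustment reduces confounding that runs through the baseline score; it does not turn preference groups into randomised ones.

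**The baseline is not fully pre-intervention.** This stands. It follows three weeks of tele-drain care, which is part of what the trial evaluates, so the adjusted contrast concerns the rehabilitation phase only.

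**Stronger readings that a reader might infer, and that the document does not support:**
- That the plan reads self-selection as a treatment effect. The trial is labelled a quasi-experimental pilot, its success criterion is attrition of 20% or less, and it makes no efficacy claim. It does not say that the observed group difference will be the planning effect for the main trial.
- That the t test loses its nominal level as such. It keeps that level for whether two preference groups differ. The rejection rates above refer to a null of no effect of rehabilitation mode.
- That the two arms are pooled or the unaffected arm is discarded. "The measurement per arm will be averaged for analysis" refers to the two repeat readings on each arm and excludes no later use of either arm.

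**Conclusion.** The concern holds as a poor choice of named method in a feasibility pilot. With groups formed by preference, neither an unadjusted exit-score test nor an unadjusted change-score test generally handles a baseline imbalance, and the plan names nothing else. The size depends on assumptions that the document does not supply. At 20 per group the exit-score distortion runs from a rejection rate close to nominal (0.09 SD, about 6%) to substantial (0.35 SD, about 19%). The upper end needs a 0.5 SD gap, a correlation of 0.7 and full enrolment without attrition, and it should not be quoted alone. The precision gain is secondary: appreciable at a correlation of 0.7, and small or absent at 0.3. The primary outcome, time spent on rehabilitation, has no baseline value, so this remedy does not reach it.

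**What to change.** 1. For each continuous secondary outcome, replace the t test with ANCOVA of the exit value on group and the pre-rehabilitation value of the same measure. Report the adjusted difference with its 95% CI.
2. With 10 to 20 per group, keep age, surgery type and, for AROM and circumference, the unaffected arm as optional sensitivity analyses.
3. Label all between-group results exploratory and non-causal. State that confounding by preference remains, and that the baseline follows the three-week tele-drain-care phase, so the adjusted contrast concerns the rehabilitation phase only.
4. Report rehabilitation time by group descriptively, with a CI for the difference.

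The cost is wording in the analysis section or analysis plan. It needs no extra patients, visits or measurements for the main model. Statistically it costs one degree of freedom, and at 10 per group with a low correlation it brings little or no gain in precision.
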